## **4.2 Secondary endpoints**

Secondary endpoints will include the following:-

1. Incidence of foetal death during treatment, defined as absence of foetal heartbeat assessed by Doppler;
2. Hypoglycaemia requiring treatment;
3. Parasite recrudescence or re-infection on day 14;
4. Parasite clearance on day 3;
5. Level of recovery of haemoglobin on day 14;
6. Fever clearance time;
7. Incidence of perinatal and neonatal mortality, assessed 4-6 weeks after due date of delivery;
8. Clinically apparent neonatal abnormality, assessed 4-6 weeks after due date of delivery;
9. Placental malaria
10. Preterm delivery
11. Other adverse events during treatment.

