of malaria in pregnancy showed no adverse effects on the mother or on her baby (McGready *et al* 2001). Following WHO recommendations (1995) artemisinin derivatives have been used for malaria treatment during the second and third trimesters of pregnancy where multi-drug resistance is likely. Whilst most of the data from treatment doses is from Asia, 287 pregnant women in the Gambia given a single dose of SP-artesunate had no increased rate of adverse birth outcomes (Deen *et al* 2001). Recent meetings of toxicologists and clinicians convened by the WHO (July 2002) reviewed all available data. Whilst there is some evidence of fetal toxicity in some animals early in pregnancy, there was felt to be no evidence from human studies contradicting proceeding with studies with artemisinin containing drugs in the second 2 trimesters of pregnancy (report in progress).

Amodiaquine also has been given to many hundreds of women in pregnancy in Africa and elsewhere, either inadvertently or deliberately, and studies have demonstrated no teratogenicity (Thet Naing *et al* 1988), although formal safety data are sparse. The WHO recommends it can be used for treatment of malaria in pregnancy (1995). Although formal side-effect studies on these combinations (SPAQ AQAS) have not yet been conducted, hence this proposal, there is sufficient data from pregnant women to justify the combinations chosen in a randomized trial which actively looks for side-effects and birth outcome in women where the drug is given after the first trimester.

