### **7 Follow up at birth and after delivery.**

- (a) Birth outcome will be recorded for all study mothers who deliver in Teule hospital (currently between 70 and 80% of those who attend antenatal clinics). This will include maternal mortality, perinatal mortality, maternal complications, and whether the new-born baby has any clinically apparent abnormalities.

- (b) Patients will be followed up at home by VHWs on day 7 after birth for kernicterus. Previous studies have demonstrated that following up at home works well in Muheza district.
- (c) Patients will be encouraged to bring their babies to Teule for routine immunisation one month after birth, and assessed for birth outcome at that point. At 6 weeks after due date, all mothers (whether giving birth in Teule or not) who have not attended will be followed up at home. Assessment at that time will include birth outcome, or a serious problem since birth such as kernicterus, and the baby will be examined for congenital abnormalities. In the case of a neonatal or maternal death a history will be taken from the main carer or any healthcare workers involved to try and ascertain the cause of death. Whenever the mother has moved from the area all possible efforts will be made to ascertain birth outcome.

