## **9 Stopping rules/discontinuation criteria (finalised after meeting of the DSMB)**

*Parasite clearance:* The study has to balance the Tanzania government's recent policy to use SP as first line drug treatment against a high SP-resistance in Muheza district. We assume that around 45% of women in the SP group will need escape medication. Since all women will be admitted to the study ward, the escape medication will be administered on time and complications arising from the use of a relatively ineffective drug should be minimal. However, if the proportion of women needing escape medication is  $\geq 40\%$  in any arm of the study, we will discontinue that arm when 50 women are enrolled which will give a confidence limit of 25-55% for the estimated treatment failure rate.

*Side effects.* All serious possible side-effects and foetal deaths will be faxed to the DSMB statistician. All other adverse events will be forwarded. The DSMB (see section on ethics) will decide on whether one arm, or the whole study, needs to be terminated. Suggested guidelines for this following the first meeting of the DSMB is that the DSMB would take note following one SAE in an arm, and consider whether an arm needed to be terminated after 2, but would review in the light of data at that stage. The DSMB wishes to be informed if there is a fall in haemoglobin of  $>4$  g/dl, OR where haemoglobin falls below 5 g/dl and these will be treated as a potential SAE, but since most such drops will be secondary to the natural history of the disease these will be noted and discussed, but treated differently from other SAEs.

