#### **2) Subject information and Informed Consent**

- a) Each woman will receive written information (in Kiswahili) about the study, which will also be explained in the presence of the witness when applicable. Sufficient time will be allowed for the woman to decide if she wishes to join the study;
- b) Women will be allowed to enquire about details of the study and any question regarding the study will be answered;
- c) The PI will ensure that the consent form has been signed and dated by the participant, attending clinician and/or witness where applicable;
- d) In the case of a patient who cannot read, an independent literate witness will attend the information session, sign and date the consent form on behalf of the patient;
- e) In case of protocol amendments, the PI will ensure that the consent form is also revised to reflect the approved amendments.

3) All drugs used in the study have been used for treating malaria in pregnancy previously (see section 6.1 for further details), although not necessarily in the combinations proposed in this study.

4) An independent Data and Safety Monitoring Board (DSMB) will be set up. This will receive reports of all adverse events, and of treatment failures to ensure it is safe to continue the trial. Exact terms of reference and provisional stopping rules will be determined in consultations between the Committee and the trial investigators.

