A SAE shall be reported within 24 hours by telephone, fax, or e-mail to the safety monitoring board. Thereafter, the PI will submit a written report describing the SAE, its onset, date of onset, type, duration, severity, cause-effect relationship to the administered drug(s), outcome and measures taken.

SAEs will be recorded in the CRFs, evaluated and discussed at the conclusion or termination of the study.

Personal data of patients will be kept confidential.

The agreement covering the use of data or analysis will be documented in writing together with the written informed consent for participation in the trial.

The PI will retain study material for an agreed period. Destruction of study material thereafter, will require a joint written authorization from interested parties.

All trial data will be recorded on the CRFs in English. Only the PI and a few authorized co-workers (as on the list of Authorized Signatory Form) will make entries.

Entries will be legible in black or blue ballpoint pen. Corrections should be made by drawing a single line through the original entry, entering the new value with initials and date next to the new entry. Completed CRFs will be dated and signed by the PI.

All clinical data will be entered into medical records. The clinical and laboratory results will be transcribed into the CRFs. SDs will be kept in a separate file from CRFs.

The clinical monitor will review all completed CRFs for completeness and accuracy before data entry into computer. Entry will have checks to identify errors and protocol violations. Request for clarifications and/or corrections on errors/violations will be sent to the PI. Analysis will be carried out after all queries have been addressed and database locked.

The PI will ensure that all study drugs are received, stored and documented. All study medications will be stored at room temperature under lock and key at the study site.

The PI will issue the study medications to the “dispensing nurse” of the study team. The dispensing nurse will account for all used and unused drug supplies. A drug accountability list will be kept in the investigator’s file. Remaining medications will be kept in the original blister packs. The nurse will keep blister packs with or without remaining drugs for inspection and validation against the drug accountability list

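### Foetal deaths go to the DSMB unconditionally, but neonatal deaths, newborn abnormality and kernicterus reach it only through a causality judgement or an undefined SAE label

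*Protocol*

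**What the plan says.** **What goes to the DSMB.** Protocol section 9, under side effects: "All serious possible side-effects and foetal deaths will be faxed to the DSMB statistician". The next sentence adds: "All other adverse events will be forwarded". As a suggested guideline, "the DSMB would take note following one SAE in an arm, and consider whether an arm needed to be terminated after 2". Item 4 of the Ethical Issues says of the DSMB: "This will receive reports of all adverse events, and of treatment failures to ensure it is safe to continue the trial". Appendix 2 adds: "A SAE shall be reported within 24 hours by telephone, fax, or e-mail to the safety monitoring board".

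**What counts as an adverse event.** Section 6.4(b) records a clinical or laboratory abnormality as an adverse event when the senior attending clinician thinks the study drug may have caused it. The causality table in the same section nevertheless has a category for events unrelated to the medication. SAE is not defined anywhere in the protocol.

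**What the trial collects on newborns.** The Summary makes birth outcome part of the safety aim. Section 6.1 defends the choice of combinations by describing "a randomized trial which actively looks for side-effects and birth outcome in women where the drug is given after the first trimester". Section 4.2 lists "Incidence of perinatal and neonatal mortality, assessed 4-6 weeks after due date of delivery" as secondary endpoint 7 and neonatal abnormality as endpoint 8. The section on follow-up at birth and after delivery plans a day-7 home visit for kernicterus and a later assessment at which "the baby will be examined for congenital abnormalities". After a neonatal death, a history is taken to look for the cause.

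**The concern.** Two kinds of birth-outcome harm are handled differently. A foetal death is sent to the DSMB statistician with no condition attached. A neonatal death, a malformation or a case of kernicterus is not named, and must first be classed as an adverse event or an SAE.

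That classification is a weak filter for these outcomes. They are found weeks to months after a course of at most three days, and a single case can rarely be attributed with confidence. A drug effect is more likely to show as a difference in frequency between randomised arms. If cases are dropped one at a time because each looks unrelated, the body that decides whether an arm continues may not have the counts needed to see that difference.

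**Working it through.** The point concerns reporting rules and rests on no figure stated in the plan. The main check sets the provisions side by side; two short calculations then show whether the gap matters.

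**1. Routes to the DSMB**

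| Event | Named in section 9? | Other route | Condition on that route |
|---|---|---|---|
| Foetal death | Yes | not needed | none |
| Large haemoglobin fall | Yes, by numerical limits | not needed | none; handled apart from other SAEs |
| Neonatal death, newborn abnormality, kernicterus | No | serious possible side-effect, or other adverse event (section 9; Ethical Issues, item 4) | clinician's opinion under 6.4(b), or the wider reading its causality table allows |
| Same | No | SAE within 24 hours (Appendix 2) | SAE not defined |

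The section on follow-up at birth contains no step that sends an event to the DSMB. The haemoglobin row is instructive: section 9 makes those falls reportable while accepting that the disease will explain most of them. The protocol therefore already uses cause-blind reporting where attribution is hard.

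**2. Could birth outcomes inform the DSMB during enrolment?**

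Inputs: entry at 14 to 34 weeks (section 5.2); assessment 4 to 6 weeks after the due date (section 4.2); due date at 40 weeks (assumed); uniform enrolment over 104 weeks (assumed from the 2-year study duration).

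- Shortest lag: (40 − 34) + 4 = 10 weeks.
- Longest lag: (40 − 14) + 6 = 32 weeks.
- Share of outcomes known before enrolment closes: (104 − 32)/104 = 69% if every lag were the longest, and (104 − 10)/104 = 90% if every lag were the shortest.

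With the original plan's 450 working days at an assumed five per week (90 weeks), the shares are (90 − 32)/90 = 64% and (90 − 10)/90 = 89%. Either way, most outcomes arrive in time to be used.

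**3. Does it matter whether these deaths count as SAEs?**

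The revised sample size is 72 per arm. It reproduces for 1% versus 15% with two-sided 5% significance, 80% power and a continuity correction (58 without the correction), and is used here only as the arm size. Twin pregnancies are excluded, so 72 women give at most 72 newborns. The documents give no neonatal death rate p, so a range is assumed.

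P(at least 2 deaths) = 1 − (1 − p)^72 − 72p(1 − p)^71

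| Assumed p | Expected deaths, 72p | P(at least 2) |
|---|---|---|
| 1% | 0.72 | 16% |
| 2% | 1.44 | 42% |
| 3% | 2.16 | 64% |
| 5% | 3.60 | 88% |

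If neonatal deaths count as SAEs, an arm can readily reach the two-SAE step on background mortality alone. If they do not count, the same arm may not reach it. The protocol does not say which applies.

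**The case against.** The strongest reply is that the DSMB is not cut off from these events. Section 9 forwards all other adverse events, the Ethical Issues section gives the DSMB all adverse events, and Appendix 2 sends SAEs within 24 hours with no causality wording in that sentence. The threshold in 6.4(b) is low, since the clinician need only think the drug might be the cause, and the causality table would have little use for its unrelated category if such events were never recorded. Staff are told to look for kernicterus and malformations, so they may well suspect the drug. Exact terms of reference are left to the DSMB and the investigators, and by-arm tables often sit in a charter.

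Much of this stands. A reader might infer from section 9 that newborn harms trigger no safety review at all; the documents do not support that, because an event judged possibly drug-related is faxed and counted. A reader might also infer from Appendix 2, which has SAEs evaluated and discussed at the end of the study, that review waits until then. That sentence follows the 24-hour report and the written report and adds to them; it does not replace them. Nor do the documents show that clinicians would usually judge these events unrelated.

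What the reply does not supply is an unconditional route. Each fallback depends on a classification that the protocol either ties to opinion or leaves undefined, and the tension between 6.4(b) and its own table means that two careful investigators could report differently.

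**Conclusion.** The point holds as a gap in a stated rule. The protocol gives foetal deaths an unconditional route to the DSMB and gives neonatal death, newborn abnormality and kernicterus only a conditional one, although birth outcome is part of its safety aim. The consequence is a possibility, not a certainty: outcomes judged unrelated case by case may not be reported, and an imbalance between arms could then be missed during enrolment.

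The number of events that would be lost cannot be estimated from the documents. The calculations show only that review during enrolment is feasible (roughly 64% to 90% of outcomes known before it closes, given a 40-week due date, uniform accrual and 90 to 104 weeks of enrolment), and that counting or not counting neonatal deaths changes how often the two-SAE step is reached (16% to 88% for assumed rates of 1% to 5%). The change should be made because it is specific, nearly free and bears on participant safety.

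**What to change.** - **Section 9:** name perinatal and neonatal deaths, clinically apparent newborn abnormality and kernicterus beside foetal deaths as events sent to the DSMB statistician whatever the suspected cause. Add a matching reporting step to the section on follow-up at birth and after delivery.
- **Definitions:** define SAE, and reconcile 6.4(b) with its causality table so that it is clear whether events judged unrelated are recorded.
- **DSMB reports:** include a by-arm listing of known birth outcomes, with the number of women whose outcome is known as the denominator.
- **Thresholds:** leave to the DSMB any review threshold, and whether these events enter the SAE count or are handled separately as haemoglobin falls are. A fixed rule based on an excess in one arm is not advisable: with 72 per arm, chance imbalances in a handful of events are to be expected.

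The cost is a few sentences of protocol text and a few more faxed forms. The DSMB, the visits and the data collection are already planned.

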### **4. TRIAL DESIGN**

#### **4.1 Primary end point**

The primary end-point of the trial will be treatment failure by day 28. This will be defined as:-

*Any of:-*

- 1) a need for rescue treatment due to clinical deterioration defined by altered sensorium, convulsions, persistent vomiting, renal impairment, respiratory distress, a fall in Hb below 7g/dl, or in cases where initial haemoglobin was less than 9 g/dl a drop of 20% from the starting Hb, at any time during admission;
- 2) persistence of fever with parasitaemia on day 3;
- 3) increasing parasite load on day 3;
- 4) failure to clear parasites on day 7;
- 5) rescue medication for recurrent malaria before day 28;
- 6) slide parasite positivity at day 28.

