### **5.2 Inclusion criteria**

A pregnant woman who has:-

*either* a positive blood smear for *P.falciparum* with at least 1000 asexual parasites/ $\mu$ L in an asymptomatic woman  
*or* any of the following symptoms within 2 days prior to consultation: history of fever; headache, vomiting, chills/rigors, and/or any of the following signs: temperature  $\geq 37.5^{\circ}\text{C}$  and  $< 39.5^{\circ}\text{C}$ , Hb  $\geq 5$  and  $< 9$  g/dl) together with *P.falciparum* parasitaemia at any density

and (in both cases) the following:

1. has no exclusion criterion (see below);
2. is 14-34 weeks pregnant on the day of attending the ANC clinic or OPD;
3. has a viable foetus, defined by presence of foetal heartbeat by sonicaid or pinnard (foetal heartbeat is not heard until 14 weeks);
4. is able to take study drugs by the oral route;
5. is able to attend stipulated days for follow up clinic and provide specimens;
6. gives informed written or witnessed verbal consent to participate by herself, and also through her parent/guardian if aged  $< 15$  years (in conformity to Tanzania Law).

Those  $> 34$  weeks are excluded because they are close to term and may deliver during the 28 day f/u period.

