*Based on the sample size of 80 women on SP alone and 240 in each of 3 combination regimens while allowing for 10% loss to follow up, a total of 900 women will be enrolled in the study. According to records at MCH for year 2000, a total of 6,880 pregnant women (approximately 20 per day) attended the antenatal clinic, of which an average of 6 per day had complaints. We assume that 3 of the sick 6 will have falciparum malaria and that 2 of them will consent to participate. Therefore, it will take 450 working days to enrol 900 women and the duration of the study is estimated to be 2 years.*

*The sample size should be adequate and sufficiently robust to detect common side effects in pregnancy. Rare side effects can only be detected in large Phase 4 and post-marketing surveillance studies. This study should provide information which can allow such studies to be undertaken.*

**Oct 2004.** Vigorous measures to protect pregnant women in the district from malaria on a general background of reduced transmission of malaria in this area have fortunately led to substantial reductions in the number attending the antenatal clinic with clinical malaria. The investigators reviewed the data from other sites, and it is clear there is still likely to be a critical shortage of data on antimalarials in pregnancy from Africa, so a trial even with an ability to detect this relatively large difference is likely to be of considerable utility to policymakers. A revised sample size has been calculated to detect a difference at day 28 from 1% (the best likely failure rate in any arm) and 15% (above which no drug could be deployed). This gives a sample size of 72 in each arm when  $\alpha$  was .05 and  $\beta$  0.8. This would be capable of detecting common, but not rare, adverse events. The trial will continue on this basis due to the public health importance of this question.

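### No stand-alone between-arm safety comparison of early haemoglobin is named: in-admission falls enter only through the primary efficacy composite, and day-14 recovery, the one named Hb outcome, has no scheduled sample.

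*Protocol*

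**What the plan says.** **Section 9, Side effects.** The DSMB would "take note following one SAE in an arm, and consider whether an arm needed to be terminated after 2". A fall of more than 4 g/dl, or an Hb below 5 g/dl, must be reported, and "these will be treated as a potential SAE". The section then sets such falls apart: "since most such drops will be secondary to the natural history of the disease these will be noted and discussed, but treated differently". The contrast is with SAEs of any other kind. The section mentions no count, rate or comparison by arm for these falls.

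**Section 4.1, item 1.** Treatment failure includes a need for rescue because of clinical deterioration during admission. One listed criterion is "a fall in Hb below 7g/dl, or in cases where initial haemoglobin was less than 9 g/dl a drop of 20" (the last figure is a percentage of baseline Hb).

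**Section 6.4.** By its heading, adverse events exclude treatment failure. Item b admits a laboratory abnormality when the senior clinician thinks the study drug might be, or is likely to be, the cause.

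**Sections 4.2 and 11.** The only stand-alone Hb outcome is the level of recovery on day 14. Adverse events are also listed for analysis, without detail.

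**Sampling.** Section 6.5 schedules haematology on admission, on day 3 (called the last drug day) and on day 7, with nothing further unless clinically indicated. Appendix 1 ticks haematology on days 0 and 7 and has no day-3 column. Section 6.6 allows blood at clinic visits only when appropriate. Section 5.4 takes Hb at withdrawal.

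**Ethical issues, item 4**, on the DSMB: "This will receive reports of all adverse events, and of treatment failures to ensure it is safe to continue the trial".

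**The concern.** Safety is an objective alongside efficacy (section 3), and a woman may enter with Hb as low as 5 g/dl (5.2). If one regimen lowers Hb in the first week, the plan as written handles the signal in three ways:

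- A fall during admission that leads to rescue counts as a failure of efficacy.
- A large fall is discussed case by case, on the presumption that malaria caused it.
- The day-3 and day-7 values collected for safety have no named safety comparison.

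The presumption cannot be checked one case at a time. Randomisation balances the disease at entry, so a difference between arms, read beside parasitological response in the same arms, is what separates a drug effect from the effect of inadequately treated malaria. That second reading matters here because section 9 says "We assume that around 45% of women in the SP group will need escape medication": an excess of falls on SP could reflect poor clearance and not toxicity.

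**Working it through.** **1. How far the primary endpoint covers the notifiable falls.** Compare section 9 (fall above 4 g/dl, or Hb below 5) with 4.1 item 1 (Hb below 7, or a 20% drop from a baseline under 9).

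- Fall above 4 from a baseline of 11 or less: 11 − 4 = 7, so the value ends below 7.
- Hb below 5 from a baseline of 6.25 or more: 0.8 × 6.25 = 5.0, so the drop exceeds 20%.
- For baselines from 6.25 to 11, every notifiable in-admission fall therefore meets the 4.1 Hb threshold. Coverage is broad, but only within the efficacy composite and only through rescue.
- Not covered: 12 to 7.5 g/dl (a fall of 4.5, not below 7, baseline not under 9), and any fall first seen at day 7, after admission.
- The reverse also occurs. From 9 to just under 7 is a fall of just over 2 g/dl. It meets 4.1 but neither limb of section 9, so it can count as an efficacy failure and never be notified as an Hb fall.

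The two section 9 limbs also measure different things. The fall needed to qualify is just over 0 at a baseline of 5, 2 at 7, and 4 at 9 or more.

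**2. Whether the named Hb outcome has data.** Day 14 lies outside the 6.5 schedule and is unticked for haematology in Appendix 1. A finger-prick smear is ticked that day. As for day 3, Appendix 2 calls the first treatment day day 0, and Appendix 1 gives drug on days 0 to 2, so the day 3 of 6.5 may be the day-2 column. That column is unticked for haematology too.

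**3. The plan's own sample size (October 2004 revision: 1% v 15%, two-sided 5%, β of 0.8 read as 80% power).**

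- Uncorrected: n = [1.96√(2 × 0.08 × 0.92) + 0.84√(0.01 × 0.99 + 0.15 × 0.85)]² / 0.14² = 57.8.
- Continuity-corrected: (57.8/4) × [1 + √(1 + 4/(57.8 × 0.14))]² = 71.3, so 72 per arm. The stated figure reproduces.

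**4. What 72 per arm gives for mean Hb change.** Detectable difference = (1.96 + 0.84) × SD × √(1/n₁ + 1/n₂). The SD is assumed to be 1.0 to 1.5 g/dl; the protocol gives none.

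| Comparison | √(1/n₁ + 1/n₂) | Detectable (g/dl) |
|---|---|---|
| 72 v 72 | 0.167 | 0.47 to 0.70 |
| 65 v 65 (10% lost) | 0.175 | 0.49 to 0.74 |
| 50 v 72 (SP stopped at 50, section 9) | 0.184 | 0.52 to 0.77 |
| 24 v 72 (if the 1:3 blocks of 6.2 still apply) | 0.236 | 0.66 to 0.99 |

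The 95% CI half-width at 72 v 72 is 1.96 × 0.167 × SD = 0.33 to 0.49 g/dl.

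**5. What it gives for the proportion with a large fall** (rates assumed; two-sided Fisher 5%, exact enumeration).

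| Rates | Power, 72 v 72 | Power, 65 v 65 |
|---|---|---|
| 1% v 5% | 8% | 6% |
| 3% v 10% | 26% | 22% |
| 5% v 15% | 42% | 37% |

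For example, 7/72 v 2/72 is 6.9 points, Newcombe 95% CI −1.5 to 16.2.

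**6. Whether the two-event guideline should apply to these falls.** P(2 or more of 72) = 1 − (1 − p)⁷² − 72p(1 − p)⁷¹, which is 16%, 64% and 88% at p = 1%, 3% and 5%. Background alone would often reach two, so section 9 is right to handle them separately.

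**The case against.** The strongest reply is that the DSMB already has what it needs. Notification under section 9 depends on the Hb value alone, with no clinician filter and no admission limit, so a notifiable day-7 fall reaches it. It also receives treatment failures, and it can stop one arm, which implies data by arm. By-arm tables and baseline-adjusted models are ordinary content for an analysis plan or a DSMB report. Much of this stands. Silence about a by-arm DSMB table is close to missing detail and would not carry the point alone.

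What remains is fixed in the protocol itself. Section 4.1 classes the fall as efficacy failure, 6.4 excludes treatment failure from adverse events, and the day-14 outcome has no scheduled sample. The 6.4 causality scale does include unrelated events, which softens the attribution filter but does not bring treatment failures back in.

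Two stronger readings are tempting, and the documents support neither. A reader might infer that early Hb has no between-arm use at all. It has one, through the primary composite and, by way of rescue, the 40% per-arm escape rule. A reader might also size the disease-driven excess on SP by scaling the failure rates of 45% and of 1% to 15%. An assumed share of failures with a fall cancels from any such ratio, and the day-28 definition includes late slide positivity, which cannot cause a first-week fall.

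**Conclusion.** The point holds as a should-fix matter. Followed as written, the plan can record a drug-induced early Hb fall as lack of efficacy. It gives the scheduled early values no safety comparison of their own, and it leaves the one named Hb outcome without routine data. It does not show that the DSMB would miss such falls or be unable to act on them.

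If the SD is 1.0 to 1.5 g/dl, a by-arm estimate of mean change is informative at this size: 0.47 to 0.70 g/dl detectable, below the 1 g/dl rise that Appendix 2 expects of an effective drug. The proportion with a large fall is for description only, with power of 8% to 42% over the assumed rates. All Hb rates and SDs here are assumptions, and an excess on SP alone would remain hard to attribute.

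**What to change.** 1. Report failures met through the 4.1 Hb clause separately from parasitological failures. Count them in the safety tables as well, whatever the attribution.
2. In sections 4.2 and 11, add a by-arm estimate with confidence interval of Hb change from baseline to day 7, and to day 3 where taken, adjusted for baseline Hb. Show the proportion meeting the DSMB definition descriptively, with the two limbs apart and baseline Hb alongside.
3. Schedule Hb with the finger-prick already taken on day 14. Align Appendix 1 with 6.5 on end-of-treatment haematology, and settle which study day that is.
4. In section 9, keep the separate handling and case discussion. Show the DSMB these falls cumulatively by arm, with women treated as the denominator, beside parasitological response. Give SP its own row and set no fixed trigger.

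The cost is protocol wording, one or two extra tables, modest DSMB reporting, and one Hb test per woman at an existing visit. The end-of-treatment sample is already required by 6.5, so aligning Appendix 1 adds nothing beyond what that section asks for.
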